### Component 3: Supervision of community-based nutrition counsellors

The aim of supervising nutrition counsellors is two-fold: 1) to reinforce theoretical knowledge, counselling and practical skills learned during training, and 2) to give support and feedback needed to address child nutrition challenges in their communities. Supervisory visits coupled with observed counselling sessions, review of home visits workbooks and discussions on feedback will be made by the research team to assess the quality of counsellors’ work. An observation checklist for individual counselling will be used to assess practice on interpersonal skills, active listening, effective use of counselling resources, offer referrals appropriately, promote problem-solving among mothers, and discuss practical solutions. Counsellors will receive a simple score of 2 = “Yes, sufficient” or 1 = “Yes, limited” if a correct practice is observed, and 0 = “None at all” if the practice is not done. Supervisory visits will take place in the villages at 2-weeks interval in the first 2 months of intervention, and thereafter visits will be made at 2-month interval.

### Component 4: Sensitisation meetings

Sensitisation meetings will be held in intervention villages in the form of presentations and discussions with selected groups likely to influence the success and sustainability of the intervention. These include family members and health facility staff.

#### Sensitising family members

The aim of sensitising family members is to improve their knowledge and attitude on child nutrition issues so as they can ensure dietary adequacy and optimal growth. A 1 to 2 hour sensitisation meeting will be held with fathers, grandmothers and older siblings of recruited infants. The structure of the meeting will consist of four parts: Intervention rationale, content and activities; why nutrition matters during the first two years of life; promoted recommendations and their role in supporting mothers; and importance of adherence to intervention for its success. The meetings will take place twice: at baseline and 6 months into the intervention.

#### Sensitising health facility staff

The aim of sensitising health facility staff is to improve their knowledge and attitude on feeding practices so as they can counsel mothers and caregivers during routine well-baby and sick-child visits. In villages where a health facility exists, two potential health workers will be nominated by their resident in-charge of the health facility to participate in sensitisation meetings. A 3 to 4 hour sensitisation meeting will take place in respective villages. At the meeting, the intervention will be outlined and its implications for community infants and young child discussed. Other topics for presentation and discussion will include why nutrition matters during the first two years of life; feeding principles and practices, use of locally available foods to make nutritious complementary meals, and key messages to share with the mothers. The meetings will take place twice: at baseline and 6 months into the intervention.

### Data collection and measuring impact of the intervention package

Procedures for the collection of information are standardised. Data collection forms (structured questionnaires, observation checklists, etc.) were translated into the local language, Kiswahili. The accuracy of the translation was checked by back translation into English. The questionnaires were pre-tested with 20 mothers in a neighbouring district to determine whether the items were adequate, clear and culturally appropriate. Revisions and modifications were applied accordingly. Data collectors will administer the forms in Kiswahili. After data collection, all filled forms will be manually checked for completeness and consistency. To enhance blinding, precise objectives of the study and village allocation to trial will not be disclosed to data collectors, nutrition counsellors will not be responsible for data collection, and data collection schedule will be randomised.

### Secondary outcomes

Secondary outcomes will include:

Mean change in weight and weight-for-length Z-scores (WLZ)Mean intake of energy, fat, iron and zinc from complementary foodsProportion of children consuming foods from 4 or more food groupsProportion of children consuming the recommended number of semi-solid/soft meals and snacks per dayMaternal level of knowledge and practice of recommended feeding and health practices

#### Anthropometry

Recumbent length will be measured to the nearest 0.1 cm using a portable wooden infant/child length board (Shorr Productions, Perspective Enterprises, Portage, Missouri) with a fixed head and sliding foot piece. Children will be weighed with light clothing to the nearest 10 g using a digital infant weighing scale (Salter model 235, CMS Weighing Equipment, London). The weighing scale and length board will be placed on a flat surface to ensure correct measurements. Each measurement will be done in duplicate and the mean value calculated. Child’s age will be recorded from the health card or birth certificate. Standardised anthropometric procedures [45] will be observed. Nutritional status indices LAZ and WLZ will be computed for each child by comparing the child’s measurements with the reference values of the WHO 2006 child growth standards using ANTHRO software v3.0.1 (ANTHRO, WHO, Geneva). Data will be collected at baseline, 9, 12 and 15 months in intervention group, whereas in control group, data will be collected at baseline, 12 and 15 months.

#### Dietary intake

Intake of specific nutrients (energy, protein, fat, iron, zinc) will be assessed at baseline and 12 months in intervention and control groups using interactive 24-hour dietary recall [46]. Mothers will be asked to recall all foods and fluids consumed by their children in the previous 24 hours. Information on time, type of meal, ingredients used, amount of total dish, and amount consumed will be documented. Amounts will be determined using a digital food balance (TANITA kitchen scale, KD-400, maximum weight 5 kg, precision 1 g), household and other common utensils (e.g. spoons, cups, bowls), and visual aids (e.g. fresh foods). Daily intake of nutrients will be calculated using the 2008 Tanzania Food Composition Tables [47]. Nutrients intake will be compared to international recommendations [48, 49].

#### Dietary diversity assessment

Information from the interactive 24-hour food recall will be used to generate number of food groups consumed by children at baseline and 12 months. At 9 and 15 months, a structured questionnaire will be used to document type of meals consumed by children in the previous 24 hours. Meals of each child will be separated into their ingredients and the number of food groups consumed generated as recommended by Dewey and colleagues [50]. The food groups includes: (1) cereals, tubers and roots; (2) legumes, nuts and seeds; (3) milk and milk products; (4) meat, fish, poultry, liver/organ meats; (5) eggs; (6) vitamin A-rich fruits and vegetables; (7) other fruits and vegetables; and (8) oils and fats. Sum of total number of food groups consumed will be generated for each child. Proportion of children consuming meals from 4 or more food groups will be determined at ages 9, 12 and 15 months in intervention villages and at 12 and 15 months in control villages.

#### Feeding frequency

Number of semi-solid/soft meals and snacks consumed per day will be collected using a structured questionnaire. Proportion of children consuming the recommended number of semi-solid/soft meals and snacks per day according to WHO [8, 51] will be determined at ages 9, 12, and 15 months in intervention villages and at 12 and 15 months in control villages.

#### Maternal knowledge of recommended practices

The intervention will promote adoption of key feeding and health care recommendations during the education and counselling sessions and home visits. Maternal recall of key recommendations will be assessed using a list of structured and open-ended questions generated from the list of key recommendations. Spontaneous recall questions will be used (e.g. What signs of illness would indicate that your child was very sick and is in need of urgent attention/treatment?), as well as prompted recall (e.g. Have you heard anything about children requiring more food and fluids during illness? This will be followed by a query of messages associated with it. Mothers will receive a simple score of 1 for each correct response and 0 for wrong response.

#### Maternal practice of key recommendations

Maternal practice of key recommendations will be assessed using a structured questionnaire and structured observation. Direct questions based on education lessons and the 11-item key recommendations will be asked to mothers. For example, a recommendation to “Wash your hands with soap before preparing meals or before feeding children,” mothers will be asked to name occasions when they wash their hands with soap, why they should wash their hands, and how they wash their hands. For recommendations on consumption of specific foods (e.g. undiluted cow’s milk, legumes, etc.), a 7-day food frequency questionnaire will be used to determine consumption frequency of the specified food items. The list of such food items will be read to mothers and asked whether they had fed those items in the previous 7 days. Pre-coded categories will include never, once per week, 2–4 times per week, 5–6 times per week, once per day, 2–3 times per day, 4 or more times per day [52].

Information on maternal recall and practice of key recommendations will be collected in intervention villages at ages 9, 12 and 15 months.

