**Table 2 Tab2:** **Key recommendations and messages for promoting optimal feeding and health practices**

1	Continue to breastfeed your child on demand, during the day and night throughout the first and second years. Breastfeed first before giving other meals.
2	Start giving soft and thick meals in addition to breast milk when child completes 6 months, then continue with mashed and semi-solid meals. Increase variety, amount and consistency of food as he/she becomes used to eating and chewing different foods.
3	Prepare a thick porridge made from a combination of cereal flours. Enrich the porridge by adding groundnuts, milk, egg or legume. Thin porridge does not contain adequate nutrients to support your baby to grow well and stay healthy.
4	Give undiluted cow’s milk to your child at least 3 times per week.
5	Cook, mash, and add one or more ingredients from legumes (e.g. beans, pigeon peas, bambara groundnuts, cowpeas) in each meal.
6	Cook, mash and feed animal source foods (e.g. eggs, beef, pork, chicken, liver, fish, sardines) at least 3 times per week.
7	Cook, mash, and feed vegetables (e.g. leafy vegetables, pumpkin, avocado) in each meal.
8	Feed your child a fruit (e.g. pawpaw, ripe banana, mango, orange) after a meal at least once per day.
9	Increase frequency of feeding meals per day (2–3 times at 6–8 months, 3–4 times at 9–11 months, 3–4 times at 12–23 months). Feed 1–2 snacks (e.g. fruit, bread with groundnut paste) between two major meals.
10	Encourage your child to eat with patience and love. Encourage a sick child to drink and eat more frequently during illness. Provide extra food after illness to facilitate quick recovery.
11	Wash your hands with soap before preparing meals or before feeding children. Wash your hands with soap after visiting the toilet, and after cleaning a child who has defaecated.
12	Learn to recognise early danger signs and symptoms of childhood diseases. Promptly take a sick child to the nearest health facility for examination and treatment.
13	Ensure that your child completes a full course of prescribed medications. Return for a follow-up visit at the health facility when required or if child’s condition is not improving.
14	Keep your home environment clean. Use preventive measures to protect your child and family from diseases.

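### The 2–4 per week answer straddles the three-per-week target for cow's milk, and conditionally for animal-source foods, so adoption can only be bounded

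*Protocol article*

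**What the plan says.** The Secondary outcomes section of the protocol article lists maternal knowledge and practice of the recommended feeding and health behaviours. The section on maternal practice of key recommendations says that, for specific foods, "a 7-day food frequency questionnaire will be used to determine consumption frequency of the specified food items". The answer options are fixed in the same paragraph: "Pre-coded categories will include never, once per week, 2–4 times per week, 5–6 times per week", then 1 per day, 2–3 per day, and 4 or more per day as the last option.

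Table 2 sets the targets for the five specific-food recommendations:

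- Recommendation 4 (milk): "Give undiluted cow’s milk to your child at least 3 times per week".
- Recommendation 5 (legumes): "Cook, mash, and add one or more ingredients from legumes (e.g. beans, pigeon peas, bambara groundnuts, cowpeas) in each meal".
- Recommendation 6 (animal-source foods): "Cook, mash and feed animal source foods (e.g. eggs, beef, pork, chicken, liver, fish, sardines) at least 3 times per week".
- Recommendation 7 (vegetables): "Cook, mash, and feed vegetables (e.g. leafy vegetables, pumpkin, avocado) in each meal".
- Recommendation 8 (fruit): once a day or more.

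Recommendation 9 gives the number of meals: 2–3 a day at 6–8 months and 3–4 a day from 9 months. Table 4 schedules maternal practice at 9, 12 and 15 months, in the intervention group alone.

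**The concern.** The questionnaire's cut-points were not set at the targets that mothers are taught. For a target of three a week, the informative boundary lies between 2 and 3, and that boundary falls inside one answer category. A mother who gives milk twice a week and one who gives it three times receive the same code. If a mother moves from 2 to 3 between the 9-month and 15-month visits, which is the change the message asks for, the form shows no change.

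What is at stake is the description of how many mothers in the intervention villages took up the advice. Animal-source food three times a week is also the example that Step 3 of the package development uses to illustrate a behavioural objective. The count is lost when the form is filled in, so a later coding rule can choose a side for the whole category but cannot recover the count.

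**Working it through.** **Inputs.** The seven answer categories come from the section on maternal practice; the targets and meal numbers come from Table 2. The plan states no figure on this point, so there is none to reproduce.

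**Step 1: classify each category.** Express each category as a range of weekly counts. It is met if its lower end reaches the target, not met if its upper end falls below it, and it straddles otherwise. The each-meal target is 7 × meals per day.

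| Answer | Weekly count | Milk, animal-source as one item (≥3) | Fruit (≥7) | Each meal, 2 meals/day (≥14) | Each meal, 3 meals/day (≥21) | Each meal, 4 meals/day (≥28) |
|---|---|---|---|---|---|---|
| never | 0 | not met | not met | not met | not met | not met |
| 1/week | 1 | not met | not met | not met | not met | not met |
| 2–4/week | 2–4 | **straddles** | not met | not met | not met | not met |
| 5–6/week | 5–6 | met | not met | not met | not met | not met |
| 1/day | 7 | met | met | not met | not met | not met |
| 2–3/day | 14–21 | met | met | met | **straddles** | not met |
| 4+/day | ≥28 | met | met | met | met | met |

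The 2–4 per week category therefore affects two recommendations, milk and animal-source foods. For legumes and vegetables it is always not met. Their difficulty is the 2–3 per day category, and it arises only at 3 meals a day (or when the meal count is not linked to the answer). Fruit is unaffected.

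**Step 2: animal-source foods asked item by item.** The food list is read out to mothers, and recommendation 6 covers several foods. If they are asked separately, their ranges add. One item at 2–4 and another at 1 gives 3–5, which meets the target. One item at 2–4 and all others at never gives 2–4, which remains ambiguous.

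**Step 3: width of the ambiguity.** Let X be the weekly count. Counting the whole category as not met gives the lower bound P(X ≥ 5). Counting it as met gives the upper bound P(X ≥ 2). True adoption is P(X ≥ 3). The gap between the bounds is P(2) + P(3) + P(4), the share of children in the category.

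No distribution is given, so take X as Poisson with mean λ, purely as an illustration: P(k) = e^(−λ) λ^k / k!. At λ = 3, P(2) = 0.224, P(3) = 0.224 and P(4) = 0.168, so the share is 0.616.

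| λ (assumed) | Share in 2–4 | Of these, exactly 2 | Lower bound | True adoption | Upper bound |
|---|---|---|---|---|---|
| 1 | 26.1% | 70.6% | 0.4% | 8.0% | 26.4% |
| 2 | 54.1% | 50.0% | 5.3% | 32.3% | 59.4% |
| 3 | 61.6% | 36.4% | 18.5% | 57.7% | 80.1% |
| 4 | 53.7% | 27.3% | 37.1% | 76.2% | 90.8% |
| 5 | 40.0% | 21.1% | 56.0% | 87.5% | 96.0% |

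**Step 4: check the remedy.** Replace 2–4 per week by 2 and 3–4, and 2–3 per day by 2 and 3. Repeating Step 1 with these categories leaves none that straddles, for any of the five recommendations, at 2, 3 or 4 meals a day.

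**The case against.** The strongest reply is that the article never names a proportion meeting the weekly target as an outcome. It does name proportions for food groups and meal frequency. For specific foods it speaks of consumption frequency, and the data analysis section plans generalised linear mixed models for discrete outcomes, with food-intake frequency as an example. Such an analysis can use the categories as recorded. That is correct, but it would not show whether the three-per-week advice was followed. A met/not-met rule may sit in a fuller document, but any such rule would still have to place the whole 2–4 category on one side.

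A second reply is that other instruments help. The dietary diversity section breaks the previous day's meals into ingredients at 9, 12 and 15 months, and the number of meals is asked separately. This gives a one-day view of the each-meal targets; it cannot give a weekly count. Direct questions and structured observation are also planned, and they might yield exact counts, but their wording is not shown.

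A third reply is that animal-source foods may be asked item by item. This stands as far as Step 2 shows: it resolves some answers and leaves others open.

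A reader might infer that adoption of four of the five specific-food recommendations cannot be determined. The documents do not support this. The weekly category reaches two recommendations, the daily one matters only at 3 meals a day, and answers outside the straddling category classify cleanly.

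**Conclusion.** The point holds within limits. For cow's milk, six of the seven answers classify cleanly and one does not, so adoption of the target can be bounded but not estimated from this questionnaire. The same is true for animal-source foods if they are asked as a group, or where the summed items stay ambiguous. For legumes and vegetables the problem is separate and applies to children fed 3 meals a day.

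The size is unknown. The Poisson figures show only that the bounds can be wide; they are not a forecast for these villages. The conclusion also assumes that the direct questions do not record weekly counts for these foods.

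A reader might also infer that the trial's comparison is biased. It is not: Table 4 collects practice in the intervention group only, so this is a within-arm description. Length-for-age, the sample size and the planned between-arm comparisons are unaffected. This is a cheap improvement worth making, not a threat to the main result.

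**What to change.** Record the number of times each listed food was given in the past 7 days. If fixed answers are preferred, split the two categories at the plan's own thresholds: 2 against 3–4 per week, and 2 against 3 per day. Ask animal-source foods so that a group total can be formed. Read the legume and vegetable answers against the child's own number of meals, which the feeding-frequency questionnaire already collects.

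The cost is a minor revision of a form that has already been translated, back-translated and pre-tested, with a brief re-check of the changed answers before first use at 9 months of age. There is some loss of comparability with the source from which the categories were taken, although the split answers can be merged back into the published ones for reporting.

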**Methods/Design:**

A parallel cluster randomised controlled trial will be conducted in rural central Tanzania in 9 intervention and 9 control villages. The control group will receive routine health education offered monthly by health staff at health facilities. The intervention group will receive a nutrition education package in addition to the routine health education. The education package is comprised of four components: 1) education and counselling of mothers, 2) training community-based nutrition counsellors and monthly home visits, 3) sensitisation meetings with health staff and family members, and 4) supervision of community-based nutrition counsellors. The duration of the intervention is 9 months and infants will be recruited at 6 months of age. Primary outcome (linear growth as length-for-age Z-scores) and secondary outcomes (changes in weight-for-length Z-scores; mean intake of energy, fat, iron and zinc from complementary foods; proportion of children consuming 4 or more food groups and recommended number of semi-solid/soft meals and snacks per day; maternal level of knowledge and performance of recommended practices) will be assessed at baseline and ages 9, 12 and 15 months. Process evaluation will document reach, dose and fidelity of the intervention and context at 8 and 15 months.

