### Objectives and hypothesis

The primary objective of the intervention trial is to implement and evaluate the effectiveness of a nutrition education package in improving infant and young child feeding practices, dietary adequacy and growth. The trial hypothesises that the nutrition education package will be more effective than the routine health education. The primary outcome will be linear growth as assessed by change in length-for-age Z scores. Secondary outcomes will include feeding practices, nutrients intake and level of knowledge on recommended practices. Results of the trial are expected to provide evidence to the effectiveness of the package in community settings and, where appropriate, recommendations to strengthen the nutrition component of health education in child health services.

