Household: headship, composition, housing, fuel for cooking and lighting, water availability, and sanitationMaternal and paternal: age, education, marital status, occupation and level of child supportChild: birth order, birth weight, early infant feeding [breast feeding, exclusive breast feeding, age at first introduction (and types) of fluids/foods], child health [place of delivery, past immunisations, morbidity and healthcare seeking, haemoglobin concentration]Child health during the intervention period○ *Immunisation status* will be verified using a child’s health card at 9 months.○ *Child morbidity and healthcare-seeking practices* within two weeks before the visit will be assessed through maternal recall of signs and symptoms related to acute respiratory infections, diarrhoea, and fever; duration and severity; treatment sought; prompt use of medication; place of treatment; type of transportation used to reach the health facility; reasons for not attending a health facility; mother’s ability to identify danger signs of childhood illness; and mother’s perceptions of appropriate care after being presented with scenarios of sick children with danger signs. Acute respiratory infections will be defined as the presence of mucopurulent nasal discharge with or without cough, difficulty breathing, fast breathing than usual, breathing with severe noise or wheezing or difficulty inhaling. Diarrhoea will be defined as three or more liquid or semi-liquid stools in 24 hours. Fever will be based on maternal report of elevation of infant’s body temperature above normal. Morbidity and healthcare seeking data will be collected at baseline and at ages 9, 12, and 15 months in intervention group, whereas the same information will be collected at baseline and at age 12 months in the control group.○ *Haemoglobin concentration* will be determined using a portable battery-operated electronic Haemoglobin Photometer (HemoCue Hb 201+, Angelhom, Sweden). Non-fasting blood samples will be obtained from a finger prick of each child between 08.00 and 10.00 hours using sterile butterfly lancets. A drop of blood will be placed in a sterile microcuvette and inserted in the machine for immediate reading. The machine will be calibrated daily with a reference microcuvette provided with the machine. A trained and skilled clinician working at the Mpwapwa District hospital will be responsible for collection of blood samples and haemoglobin determination. Haemoglobin concentration will be assessed at baseline and age 12 months in both intervention and control groups. Children found to be anaemic (haemoglobin concentration below 11.0 g/dl) during the assessments will be referred to the nearest health facility for treatment free of charge, and later, closely followed up to monitor compliance to treatment and advice.Seasonality: pre-harvest, harvest, post-harvest and rainy or dry season

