**Measurements**										
Covariates	X^I+C^									
Child anthropometry	X^I+C^			X^I^			X^I+C^			X^I+C^
Child feeding practices (frequency, diversity)	X^I+C^			X^I^			X^I+C^			X^I+C^
Child food intake (24-hr recall)	X^I+C^						X^I+C^			
Child morbidity & healthcare-seeking	X^I+C^			X^I^			X^I+C^			X^I^
Child haemoglobin concentration	X^I+C^						X^I+C^			
Maternal recall and practice of feeding recommendations				X^I^			X^I^			X^I^
Process evaluation data			X^I+C^							X^I+C^

^**a**^Baseline. ^**b**^Follow-up 1. ^**c**^Follow-up 2. ^**d**^End of intervention. X^I+C^ Measurements taken in Intervention and Control groups; X^I^ Measurements taken in Intervention group alone.

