### Data management and analysis

Data will be entered in Epi-data version 3.1 and consistency analysed by range checks of data values. Data will be analysed using STATA release 12.0 (STATA Corporation, Texas, 2007). Frequency distributions will be run to identify outliers. Impact evaluation data will be compared between intervention and control villages using hierarchical or multi-level models and presented at the cluster and individual levels. The methods will provide adjustment for potential covariates and confounders at the cluster and individual levels. Data will be analysed by intention to treat. Linear mixed models will be used for continuous outcomes (e.g. growth parameters) with cluster, household, and child as random effects to account for clustered observations. Generalised linear mixed models will be used for discrete outcomes (e.g. frequency of specific food intakes, practices, etc.). Random effects logistic regression analyses, taking clustering into account, will be used where appropriate. Values of p < 0.05 will be considered statistically significant.

The process evaluation data will use both inductive and deductive approaches [55] to analyse qualitative data. The data will include structured observation checklists, in-depth interviews, and documents. From these, frequent, major, or significant themes inherent in raw data will be identified and coded. After coding, the transcripts will be entered in and analysed using NVivo version 10 (QSR International, Australia). Content will be analysed in terms of countable concepts/objects e.g. descriptive statistics, or in the broadest terms (e.g. majority, some, very few). Direct quotations from the group discussions will also be provided. Key analytical categories will be identified and interpreted to explore all aspects of intervention delivery, identify factors contributing to intervention success or failure, if intervention results have been affected by implementation process, and document encountered barriers. Within the intervention group, outcomes will be compared between groups of people with high and low scores for a process evaluation characteristic.

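### Maternal knowledge and practice is a secondary outcome of the randomised comparison, but its instrument is scheduled only in intervention villages and not at baseline, so no between-arm effect on it can be estimated

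*Protocol article*

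**What the plan says.** Objectives and hypothesis sets a comparative aim: "The trial hypothesises that the nutrition education package will be more effective than the routine health education". It then names the supporting outcomes: "Secondary outcomes will include feeding practices, nutrients intake and level of knowledge on recommended practices". The Secondary outcomes section has five entries, and the last is maternal knowledge and practice of the feeding and health recommendations. Data management and analysis gives the analysis for effect data: "Impact evaluation data will be compared between intervention and control villages using hierarchical or multi-level models".

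Maternal knowledge of recommended practices describes spontaneous and prompted recall questions, scored 1 or 0. Maternal practice of key recommendations adds direct questions (hand washing is the example), a 7-day food frequency questionnaire and structured observation. That section closes with the schedule: "Information on maternal recall and practice of key recommendations will be collected in intervention villages at ages 9, 12 and 15 months".

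In Table 4 the row "Maternal recall and practice of feeding recommendations" carries the intervention-only symbol at months 9, 12 and 15 and nothing at month 6. The footnote defines that symbol: "Measurements taken in Intervention group alone".

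The abstract gives a different schedule, with no limit by arm: "maternal level of knowledge and performance of recommended practices) will be assessed at baseline and ages 9, 12 and 15 months".

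**The concern.** A secondary outcome of a superiority trial needs a value in each arm. Here the comparator has none. Control knowledge cannot be taken as zero, because the Trial profile text says control mothers attend routine sessions that include child feeding. Without a baseline, not even the intervention arm's starting level is known.

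What remains is a series in one arm from 9 to 15 months. It begins after the first education session and after home visits have started, and it mixes the package with the child's age, the season and routine education. The Discussion accepts that self-reported recall may overstate behaviour. With no control arm there is nothing against which to judge that error.

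The stake is mainly explanatory. If growth does not differ between arms, the trial could not say from this outcome whether mothers' knowledge and practice failed to change, or changed without affecting growth.

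**Working it through.** No sample size or power figure is involved, so the check sets the schedule statements side by side.

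**Step 1. What Table 4 and the methods text schedule** (I = intervention only, both = both arms, – = none):

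| Measure | Baseline | 9 m | 12 m | 15 m |
|---|---|---|---|---|
| Anthropometry | both | I | both | both |
| Meal frequency, food groups | both | I | both | both |
| 24-hour dietary recall | both | – | both | – |
| Morbidity and care-seeking module | both | I | both | I |
| Maternal recall and practice | – | I | I | I |

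The last row is the only one without a single two-arm occasion. Methods text and table agree on it, so it is not a slip in one place or a fault of table extraction.

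**Step 2. Count.** Two arms at four ages give 2 × 4 = 8 cells. For maternal recall and practice, 3 are filled (intervention at 9, 12 and 15 months) and 8 − 3 = 5 are empty: all 4 control cells and the intervention baseline. None of the 297 infants planned for the control arm (9 villages × 33) has a mother scheduled to answer the instrument.

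**Step 3. What can be estimated.** Let I(t) and C(t) be the arm means at age t.
- Between-arm difference, I(t) − C(t): 1 of 2 terms is observed at 9, 12 or 15 months.
- Difference in change from baseline, [I(t) − I(6)] − [C(t) − C(6)]: 1 of 4 terms is observed.
- Change within the intervention arm from before the package, I(t) − I(6): 1 of 2 terms is observed.

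Only changes such as I(15) − I(9) are estimable, and they are not effects of the package. The multilevel models cannot help, because the control records would not exist.

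**Step 4. Other possible sources of control data.**
- Other measurements includes, within the morbidity module, "mother’s ability to identify danger signs of childhood illness; and mother’s perceptions of appropriate care after being presented with scenarios". That module is given in both arms at baseline and 12 months. It overlaps the recall example about signs of serious illness and the care-seeking entries in Table 2, but not most of the list.
- Food groups and meal frequency are measured in both arms, but as secondary outcomes in their own right.
- Process evaluation in control villages draws on village leaders and health workers, not on mothers.

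So the recall score, the hand-washing questions, the 7-day food frequency items and the structured observation have no control value.

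**Step 5. The abstract.** Its baseline assessment of this outcome contradicts both the methods text and Table 4.

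**The case against.** The strongest case against has four parts.

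*Two-arm data on related behaviour exist.* This stands in part. A reader might infer that the trial can say nothing about mothers' knowledge in the control arm, or that no baseline interview touches it. The danger-sign and appropriate-care items refute that, and the diet and meal-frequency outcomes cover some of the same behaviour. They do not replace the outcome as listed: the first are filed under other measurements, and the second are separate outcomes.

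*It is really a process measure.* Table 3 does count mothers' recall of key behaviours as dose received. But the abstract, the objectives and the secondary outcome list also call knowledge or practice an outcome. The two uses need separating.

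*The abstract is shorthand.* Largely fair. The same sentence gives one schedule for every outcome, although controls have no 9-month anthropometry and dietary intake is taken only at baseline and 12 months. The wording is still wrong and should be corrected, but it is not evidence that a two-arm collection was intended.

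*Knowledge is not in the hypothesis.* Correct. A reader might infer that knowledge forms part of the tested hypothesis or is the stated first step of the causal pathway. The hypothesis sentence does not name it, the conceptual framework is in an additional file that is not shown, and the theory section speaks of intentions. The point needs neither claim: a listed secondary outcome and a planned between-arm comparison are enough.

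A reader might also take the mismatch between 11 recommendations in the practice section and 14 in Table 2 as a conflict in the scoring. The only 1/0 score is defined for recall, and that section gives no number of items. The figure of 11 belongs to the practice questions. It is a separate labelling inconsistency.

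**Conclusion.** The concern holds for the recall and practice instrument as defined. It has 3 scheduled occasions in the intervention arm, 0 in control and 0 at baseline, so neither an effect against routine education nor a change from before the intervention is estimable. The gap lies in data collection, and an analysis plan could not repair it.

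Its reach is one of five listed secondary outcomes. The primary outcome, the sample size and the other four secondary comparisons are unaffected. This should be fixed, but the trial's main conclusion does not depend on it.

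The conclusion assumes that Table 4 and the methods text state the intended schedule, which their agreement supports. It also assumes that the danger-sign items are asked whenever the morbidity module is given.

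**What to change.** **Preferred.** Give the same recall and practice questionnaire, including the 7-day food frequency items, to control mothers at the 12- and 15-month visits. Add it at baseline in both arms if that is still feasible; the trial was due to start in September 2014 and the article is dated October 2014. Even without a baseline, the control data at 12 and 15 months would give a randomised comparison.

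**Cost.** Both arms are already visited at baseline, 12 and 15 months, so the questionnaire adds interview time but no visit. Prompted questions may cue control mothers to the messages, and a baseline round could cue both arms. Asking spontaneous items before prompted ones and reporting the two separately would limit and expose this. Structured observation may need more resources than the questionnaire. It can stay in the intervention arm if it is labelled as such and kept out of the between-arm comparison.

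**Otherwise.** Take maternal knowledge and practice off the list of secondary effectiveness outcomes and report it as an intervention-arm indicator of dose received, as Table 3 already does for recall. This costs nothing in the field, but gives up any comparative statement on this outcome.

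**In either case.** Correct the abstract's schedule for this outcome. As a separate minor item, reconcile the 11 recommendations in the practice section with the 14 in Table 2 and state which ones the practice questions cover.
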